### Materials and measures

#### Questionnaires and clinical assessments

Assessments are performed by trained and liscensed masters- or doctoral-level clinicians who are blinded to the treatment. Clinical outcome measures will include the Clinician Affective Reactivity Index (CL-ARI [33];) to measure changes in irritability, and the Clinical Global Impressions-Severity (CGI-S) and CGI-Improvement (CGI-I) scales to measure overall illness severity and improvement [14]. Child- and parent-reported irritability will also be assessed using the child and parent-report versions of the ARI. The CGI-S will be the primary indicator of illness severity in analyses. Secondary analyses may also explore patterns of change and predictors of improvement based on the ARI, which includes not only the clinician but also the parent and child reports.

The CGI-S assesses the severity of psychopathology (here, irritability) on a 1-7 Likert scale where 1 = normal, not at all ill, and 7 = among the most extremely ill patients [14]. The CGI-I assesses change from the start of treatment on the same 7-point Likert scale, where 1 = very much improved and 7 = very much worse.

The CL-ARI is a reliable and valid measure comprising three subscales for temper outbursts, irritable mood between outbursts, and impairment [33]. Items are scored on Likert scales where higher scores indicate more severe, longer duration, and greater frequency of outbursts, mood, and impairment. Similarly, parent- and child-report versions of the ARI (six symptom items and one impairment item) show excellent internal consistency across samples (A [89, 91].).

#### Psychophysiology

The validity of psychophysiological measures is enhanced when they are measured during psychotherapeutic sessions that model the context in which individuals manifest their most severe symptoms through exposures [98]. We will record in-vivo psychophysiology using the Empatica EmbracePlus, a research-grade wearable biosensor that continuously collects and stores electrodermal activity (EDA; galvanic skin response) and photoplethysmography (PPG; HR/HRV). PPG is an optical technique used to measure blood volume changes in the microvascular bed of tissue [2]. The Empatica EmbracePlus uses two sets of photodiodes, each containing green and red LED operation wavelengths, to measure the light differences between oxygenated and non-oxygenated peaks. The Empatica EmbracePlus is an upgraded version of the Empatica E4, which has been validated against gold-standard tools for measuring HR and HRV. It is also valid and reliable for measuring HR and HRV in youth from clinical and non-clinical populations [85]. More broadly, previous studies have provided support for the use of wearable biosensors, like the Empatica devices as well as the Apple Watch and Fitbit, to provide valid and reliable indices of HR and HRV [39, 56, 66, 102]. The Empatica devices are supported by empirical research not only in adults but also in youth and provide users access to raw data from which HRV metrics can be derived in an event-related fashion. Empatica is unique from other devices in that participant data is fully anonymized and data loss is minimized due to onboard memory, onboard data processing, and continuous data streaming. In addition to EDA and PPG, Empatica devices measure skin surface temperature using thermopile and physical activity via three-axis accelerometry.

All in-person exposure sessions will occur in the same clinical space with a fixed ambient temperature. Participants will be seated during recordings, except for exposures that require them to move about the space. Participants will be asked not to consume caffeine before their visits and will be offered water to consume before the session begins. Participants will also be asked to wash their hands to ensure a clean surface for recording from the skin.

### Sample size and power analysis

The sample size for the overarching multiple baseline trial of exposure-based CBT was previously determined by [73] using pilot treatment data [47] and established a priori as n = 40. Based on preliminary data from n = 7 participants, n = 40 achieves power = 52.7% at alpha=0.05 for hypothesis 1, power = 29.7% at alpha = 0.05 for hypothesis 2, and power = 31.0% at alpha = 0.05 for hypothesis 4. However, given that these power analyses were based on a small pilot sample, they may be unreliable. A similarly designed study of changes in HR and HRV over the course of CBT identified significant effects in a sample of n = 43 [25]. Data from the present study will be used to inform the design of higher-powered studies to further explore the mechanistic predictors and underpinnings of this novel treatment.

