### Summary and Hypotheses

Psychophysiology has played a role in distinguishing the phenotype of clinically impairing irritability, whereby youth with clinically impairing irritability report more arousal during an affective task [81]. As highlighted above, elevated arousal and decreased regulation at the level of the ANS are broadly implicated in psychopathology, including irritability. Probing variation in arousal and regulation as measured by HR, HRV, and EDA has the potential to elucidate mechanisms underlying exposure-based treatment based on principles of extinction, prediction of individual treatment response, and evaluation of treatment efficacy.

The aim of this proposed study is to assess in vivo psychophysiology—HRV, HR, and EDA—across in-person exposure-based CBT sessions for youth with clinically impairing irritability. The trial will include youth requiring treatment for a primary concern of severe and impairing irritability in multiple domains that cut across DSM-5 diagnostic categories. Our goal is to identify potential putative psychophysiological mechanisms of treatment efficacy. We consider three psychophysiological signals, as they are differentially regulated and represent variant psychological manifestations [62].

Our primary hypotheses are the following: (1) HRV will show an increase over time across sessions, reflecting improved regulation; (2) HR will show a reduction over time between sessions, reflecting decreased arousal; (3) EDA will show a reduction over time between sessions, also reflecting decreased arousal; and (4) these changes will each be associated with measurable improvement in symptoms over the course of treatment.

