### Data analysis

Extensive details of data management procedures can be found in Naim et al., 2021 and [69]. All participant data is de-identified using a numeric code to ensure confidentiality before, during, and after the trial. Only approved staff at the study site (National Institute of Mental Health) will have access to data. Estimates for HR, HRV, and EDA will be calculated as the session average for each individual across all sessions. Given the tendency of physiological data to be non-normally distributed, we will log-transform HR, HRV, and EDA data as necessary [55]. Questionnaire data will also be screened for normality and univariate outliers.

Multilevel models will be fit. Sessions (time; level 1) will be nested within person (level 2). Psychophysiological variables (HR, HRV, and EDA) from session 1 will be included at both levels 1 and 2 to account for the effects of individual differences at baseline on the intercept and slope, allowing us to test whether individual differences are predictive of treatment response within this model. Linear, quadratic, and cubic fits will be compared to determine the best-fitting model of change over treatment. First, we will sequentially fit models with psychophysiological indicators (HR, HRV, or EDA) from each of the five in-person exposure sessions defined as the outcome variable to assess change over time. Second, we will model severity of irritability based on the CGI as the outcome variable, and psychophysiological variables will be grand mean centered and entered as predictors at level 2 to assess the relation between change in psychophysiological parameters over time and irritability at post-treatment, 3-month follow-up, and 6-month follow-up. Missing data will be assessed for systematic loss and will be handled using full information maximum likelihood, which can handle both missing data and unequal time between measurement intervals [38]. We will use the Bonferroni-Holm method to correct for multiple comparisons.

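### Power is stated at an unadjusted 5% level although Bonferroni-Holm will be applied, and primary hypothesis 3 has no figure; if the Holm family spans the primary hypotheses, the stated powers are too high

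*Protocol article*

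**What the plan says.** The Summary and Hypotheses section lists four primary hypotheses: HRV rises, HR falls and EDA falls across sessions, and each change goes with clinical improvement. The third reads "3) EDA will show a reduction over time between sessions, also reflecting decreased arousal". The fourth says that "these changes will each be associated with measurable improvement in symptoms over the course of treatment", so it covers three signals.

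The Sample size and power analysis section takes the sample size from the overarching trial ("established a priori as n = 40"). From seven pilot participants it then reports that "n = 40 achieves power = 52.7% at alpha=0.05 for hypothesis 1, power = 29.7% at alpha = 0.05 for hypothesis 2". The fourth hypothesis is given 31.0%, again at the 0.05 level. Hypothesis 3 has no figure, and hypothesis 4 has a single figure with no signal named. The section warns that the figures may be unreliable because the pilot was small, and says that the study's data will inform better-powered work.

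The Data analysis section states: "We will use the Bonferroni-Holm method to correct for multiple comparisons". It does not say which tests form the family.

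**The concern.** The power section and the analysis section describe different decision rules. Under Holm, a hypothesis is tested at the full 0.05 only when every other member of its family has already been rejected. With single-test powers of 30-53%, that seldom happens. A power computed at 0.05 is then the power of a test that will not usually be performed.

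What is at stake is how a non-significant result is read. A reader who takes the HR figure at face value would think the study had about a 30% chance of detecting the pilot-sized effect. Under Holm over four hypotheses that chance is roughly 16-21%. For EDA the reader has no figure at all, although EDA change is declared primary alongside the others.

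**Working it through.** **Inputs.** From the power section: n = 40; alpha = 0.05 for each hypothesis; powers 0.527 (H1), 0.297 (H2) and 0.310 (H4). From the hypotheses section: four primary hypotheses, the fourth covering three signals. From the analysis section: Holm, family undefined. The article gives no effect size, variance, intraclass correlation, sidedness or power model, so the stated powers cannot be reproduced from first principles. They are taken as given, and only the change of alpha is examined.

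**Step 1: implied effect.** For a two-sided test (an assumption), the noncentrality is δ = z(0.975) + z(power):

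- H1: 1.960 + 0.068 = 2.028
- H2: 1.960 − 0.533 = 1.427
- H4: 1.960 − 0.496 = 1.464

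Putting these back into Φ(δ − 1.960) returns 52.7%, 29.7% and 31.0%, as it must.

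**Step 2: power at the first Holm step.** With m tests in the family, the smallest p-value is compared with 0.05/m, and power is Φ(δ − z(1 − 0.05/(2m))). For m = 4 the critical value is 2.498:

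- H1: Φ(2.028 − 2.498) = 31.9%
- H2: Φ(1.427 − 2.498) = 14.2%
- H4: Φ(1.464 − 2.498) = 15.1%

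These are lower bounds, because Holm relaxes the threshold after each rejection. Even for m = 2 the first-step values are 41.5%, 20.8% and 21.8%. A noncentral t version with 39 degrees of freedom lowers the values by at most about 1.4 points. A one-sided version at 0.0125 gives 29.8%, 12.9% and 13.7%.

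**Step 3: full Holm over the four primary hypotheses.** Test statistics were simulated (400,000 draws per scenario) as normal with means δ and a common correlation of 0, 0.3 or 0.6. The H3 effect is unknown, so it was varied: null, equal to H2, equal to H1, or 80% powered.

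| Hypothesis | Stated | Holm, m = 4 (range over scenarios) | Shortfall, points |
|---|---|---|---|
| H1 (HRV) | 52.7% | about 33-37% | about 16-20 |
| H2 (HR) | 29.7% | about 16-21% | about 9-14 |
| H3 (EDA) | none | not computable | – |
| H4 (symptoms) | 31.0% | about 16-22% | about 9-15 |

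The low end comes from a null H3, the high end from an 80%-powered H3 with correlation 0.6. The chance that all four p-values fall below 0.05 was 0.2-16% across the scenarios, which is why the full 0.05 level is seldom reached.

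**Step 4: Holm only within a hypothesis.** H1 and H2, taken as one test each, stay at 52.7% and 29.7%. H4 holds three tests. Giving each signal δ = 1.464 (equal effects, an assumption) and simulating Holm over the three gives 19.4% at correlation 0, 20.2% at 0.3 and 21.0% at 0.6, against the stated 31.0%.

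**The case against.** The strongest reply is that the family is undefined. The article says only that multiple comparisons will be corrected, and the definition may sit in an analysis plan that is not shown. If Holm works within each hypothesis, the H1 and H2 figures are right as printed. This stands, and it makes the size of the loss conditional. It does not clear H4, which loses about 10-12 points on that reading, nor does it supply H3.

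Second, each figure carries its alpha, and none has been shown to be miscalculated. This also stands. A reader might infer an arithmetic error, but the documents give no inputs from which one could be shown.

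Third, the article already reports powers well below usual targets, calls them possibly unreliable, and explains that the overarching trial fixed n. Pilot uncertainty is indeed larger than the alpha effect. If noncentrality scales with √n, the H1 effect is 2.028/√40 = 0.32 with a standard error of about 1/√7 = 0.38, so its 95% interval includes zero. This lowers the severity. But small-pilot error can go either way, whereas the multiplicity correction can only reduce power, and the caveat does not mention it.

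Some stronger readings are tempting. One could count 12 tests (three change tests plus three signals at three CGI times) and quote first-step power of about 20% for H1 and 8% for H2 and H4. The article does not define that family, and first-step values understate Holm. One could also ask for the comparison with the n = 43 study to be deleted, for hypothesis 1 to become the only primary test, or for null results to be read only from confidence intervals. These are preferences. The article does not offer the n = 43 study as a power calculation, and ranking hypotheses by power would rest on seven participants.

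**Conclusion.** The point holds conditionally. The stated powers belong to unadjusted tests, while the plan calls for Holm-adjusted ones. If the family spans the four primary hypotheses, power is about 33-37% rather than 52.7% (H1), 16-21% rather than 29.7% (H2) and 16-22% rather than 31.0% (H4). If Holm is confined within hypotheses, only H4 changes, to about 19-21%. The sizes rest on two-sided tests, a normal approximation, an H3 effect between null and 80% powered, correlations of 0 to 0.6, and, in the within-hypothesis case, equal effects for the three signals.

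The missing H3 figure is a separate gap. It does not make the other three wrong, though H3 would count in a family of primary hypotheses. A reader should not infer that the figures are miscalculated or that the study conceals low power. Severity is moderate.

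**What to change.** In the Data analysis section, state which tests form the Holm family. In the Sample size and power analysis section:

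- restate power under that rule, or label the present figures as unadjusted and print the Holm-adjusted values beside them;
- add a figure for hypothesis 3, or say why none can be computed;
- say which signal the hypothesis 4 figure refers to.

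The cost is a few sentences, a short recalculation and less favourable published figures. The sample size and data collection are untouched.

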### Preprocessing

#### HR/HRV

Blood volume pulse (BVP) data collected by the EmbracePlus is continuously analyzed by proprietary algorithms to extract digital biomarkers, including inter-beat intervals for measuring of HRV. Inter-beat intervals (IBIs) reflect the time between successive R-waves (i.e., RR time intervals) from ECG readings; for PPG, IBI reflects the time interval between successive pulsations, i.e., the pulse wave. Both R-waves and pulse waves serve as proxy measures of arterial depolarization resulting from SA-node action potentials. Because P-wave signal-to-noise ratio is poor for ECG, R-waves will be used instead. For PPG, the pulse wave, which proceeds the QRS complex (reflecting the ventricular contraction of the heart) by a slight delay, will be used. Data is sampled at a rate of 64 Hz.

We will use Kubios HRV Scientific to preprocess IBI data output from Empatica (derived from the BVP signal). Kubios is considered the gold-standard software for HRV analysis in both research and professional settings [95]. For each participant, sex, age in years, height in centimeters, weight in kilograms, resting HR in beats per minute, and maximum heart rate (the maximum HR value from the participant’s HR file exported from Empatica) will be entered into Kubios. Automatic noise detection will not be performed, and no noise segments will be removed or edited in Kubios since Empatica already removes erroneous peaks due to motion artifacts with their algorithm when calculating IBI. Additionally, motion artifacts may be induced by the exposures themselves, which is the clinical condition of interest. Finally, one study found that the highest validity was achieved when automatic noise detection and artifact removal were not used [85]. To mitigate excessive noise and motion artifacts, we will apply a wristband over the Empatica device to reduce light interference and participant preoccupation. We will use Kubios’s automatic beat correction and will record the number and percentage of corrected beats to potentially control for in analyses. Additionally, we will calculate the area under the curve as an indicator of overall session motion (based on actigraphy data recorded by EmbracePlus) and examine whether motion significantly differs within and between participants, to be considered as a possible covariate in analyses. The following data points will be extracted from Kubios: mean and standard deviation of heart rate (in beats per minute), RR time intervals (in milliseconds), minimum and maximum heart rate (in beats per minute), SDNN (in milliseconds), and RMSSD (in milliseconds). There are several metrics for HRV that map onto different physiological features. The RMSSD is a time-domain measure of cardiovascular activity [107]. The standard deviation of the normal-to-normal beat interval (SDNN) is another time-domain measure that captures the overall adaptability and flexibility of the system [55]. We will focus on SDNN as the primary indicator of HRV for this study. RMSSD will also be considered as a secondary indicator. We will only explore components from the time-varying domain of the signal, given the shorter duration of our recordings (1 hour or less treatment sessions) and the method of recording (PPG, as opposed to ECG).

#### EDA

We will use LedaLab to preprocess EDA data output from Empatica. Low- and high-pass filters will be applied to ensure that all data is within acceptable physiological ranges (0.01 to 100 microsiemens) following an adapted quality assessment protocol for ambulatory EDA data before moving on to analysis [49]. Empatica EDA is sampled at a rate of 4Hz. We will derive summary statistics of SCL (the average level of arousal across the entire session), change in SCL (magnitude and slope), SCR (range and maximum amplitude from the session), and number of SCR per minute.

### Data analysis

Extensive details of data management procedures can be found in Naim et al., 2021 and [69]. All participant data is de-identified using a numeric code to ensure confidentiality before, during, and after the trial. Only approved staff at the study site (National Institute of Mental Health) will have access to data. Estimates for HR, HRV, and EDA will be calculated as the session average for each individual across all sessions. Given the tendency of physiological data to be non-normally distributed, we will log-transform HR, HRV, and EDA data as necessary [55]. Questionnaire data will also be screened for normality and univariate outliers.

Multilevel models will be fit. Sessions (time; level 1) will be nested within person (level 2). Psychophysiological variables (HR, HRV, and EDA) from session 1 will be included at both levels 1 and 2 to account for the effects of individual differences at baseline on the intercept and slope, allowing us to test whether individual differences are predictive of treatment response within this model. Linear, quadratic, and cubic fits will be compared to determine the best-fitting model of change over treatment. First, we will sequentially fit models with psychophysiological indicators (HR, HRV, or EDA) from each of the five in-person exposure sessions defined as the outcome variable to assess change over time. Second, we will model severity of irritability based on the CGI as the outcome variable, and psychophysiological variables will be grand mean centered and entered as predictors at level 2 to assess the relation between change in psychophysiological parameters over time and irritability at post-treatment, 3-month follow-up, and 6-month follow-up. Missing data will be assessed for systematic loss and will be handled using full information maximum likelihood, which can handle both missing data and unequal time between measurement intervals [38]. We will use the Bonferroni-Holm method to correct for multiple comparisons.

In addition to the dimensional models described above, wherein irritability and change in irritability are conceptualized continuously, we will also fit dichotomous treatment response models. Individuals will be classified as either high or low responders per the methodology described in [60]. High responders will be defined as those individuals who demonstrate a 50% or greater reduction in irritability based on the CGI at post-treatment assessment. Multilevel models will be fit as described above, with responder status as the outcome variable.

Should our primary hypothesis testing reveal changes in arousal (HR/EDA) and regulation (HRV) over the course of in-person exposure sessions, we will perform post hoc exploratory analyses to investigate the temporal relationship between psychophysiology and change in symptoms over the course of treatment using cross-lagged panel modeling. To capture weekly variation in symptoms, we will use the CGI rated at each exposure session. A random intercept cross-lagged panel model (RI-CLPM) will be specified in R using the lavaan package [82]. Four components will be specified: (1) a between component, consisting of random intercepts; (2) within-person fluctuations; (3) the lagged regressions between within-person components; and (4) covariances of the within and between components [68]. Within-person variables will be mean-centered.

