### Participants

Participants will be recruited locally (Maryland, District of Columbia, Virginia; USA) via mailings to selected physicians, announcements in newsletters, contacts with support groups and approved websites, advertisements and animated videos on social media, flyers and ads in public settings, and targeted mailings to households with children. We will follow n=40 youth (all genders; ages 8-17) over 6 in-person exposure sessions as part of a multiple-baseline trial of 12 weeks of exposure-based CBT for youth with clinically impairing irritability [73]. All participants and their legal guardians will provide informed assent (youth)/consent (parents/guardians). Eligible youth will be English-speaking, willing and able to provide informed assent with parental/caregiving informed consent, and present with at least one of two core symptoms of DMDD: abnormal mood or increased reactivity to negative emotional stimuli, with severe impairment in one domain (home, school, peers) and at least mild impairment in another, or moderate impairment in at least two domains [73]. Given the transdiagnostic nature of irritability, participants may have a primary diagnosis or comorbid diagnoses of DMDD, oppositional defiant disorder (ODD), ADHD, anxiety disorder(s), or other related disorders. Symptoms and diagnoses for inclusion and exclusion criteria will be established using the Kiddie-Schedule for Affective Disorders and Schizophrenia Present and Lifetime Version [45] with the additional DMDD supplement. Exclusion criteria include: (1) meeting current or past criteria for bipolar I/II disorder or any psychotic disorder; (2) persistent depressive disorder or current major depressive episode, PTSD, autism spectrum disorders (assessed using the Development and Well-Being Assessment [27], the Social Responsiveness Scale [18], the Social Communication Questionnaire [84], and the Children’s Communication Checklist-Second Edition [8, 76]; (3) IQ less than 70 as assessed by the Wechsler Abbreviated Scale of Intelligence (WASI; Vocabulary and Matrix Reasoning Scales) [106]; (4) a significant general medical or neurological condition; (5) meeting criteria for alcohol or substance use disorder within the last three months; and (6) conditions or life situations that would interfere with the participant’s ability to participate in treatment. Participants with past major depressive disorder will not be excluded. Given the parameters of the overarching clinical trial, participants taking medications (e.g., serotonin-selective reuptake inhibitors, anticholinergics, amphetamines, allergy medications, etc.) that could impact cardiovascular and electrodermal activity will not be excluded. Rather, medication use will be considered as a candidate covariate in analyses. Enrolled participants’ medications (if any) will be written by a psychiatrist at the National Institute of Mental Health working with the study team, and no changes in medication will occur during treatment unless there is an acute clinical need. Eligible consented participants will be randomized to a staggered start schedule as part of the multiple-baseline design, with either a two-, four-, or six-week baseline period. All study visits will occur at a single site, at the National Institute of Mental Health in Bethesda, MD.

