
### Study design

The data for the present study come from a randomized multiple baseline trial of exposure-based CBT. Each participant is randomized to 2, 4, or 6 weeks of baseline observation prior to treatment beginning. This design controls for the effects of time and regression towards the mean. Randomization is performed in blocks of 10 participants with a 1:1 within-block ratio. The assignment sequence was created via a computer-based random number generator. Clinicians conducting assessments (see below) are blinded to the trial phase from commencement of the baseline period, and the blind will not be broken for the entire cohort until the completion of the trial. The exposure-based CBT protocol will consist of twelve weekly sessions. Sessions are administered by two expert clinical psychologists. In-person exposure sessions (~30-45 minutes) will occur at weeks 5-10 in the protocol. Peripheral psychophysiological data will be collected during these six in-person exposure sessions. The main outcomes we plan to assess are changes in HR, HRV, and EDA over the course of exposure sessions and relations between changes in psychophysiological data and clinical symptoms. Clinical symptoms will be assessed weekly by clinician raters, including at mid-treatment, post-treatment, and 3- and 6-months post-treatment follow-up. Group supervision is conducted by the treatment developer and clinicians rate themselves on adherence after each session in order to improve adherence and minimize drift. Patients who request to discontinue or whose condition worsens (as determined by the clinical team and PI) may meet criteria for discontinuation. All participants are informed of their ability to discontinue at any time for any reason without the loss of benefits to which they are other entitled. For more extensive details regarding the intervention, please see Naim et al., 2021 and [69].

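### Six sessions are recorded but five are modelled, and session 1 is also a predictor: the plan must say whether session 1 is an outcome, because each answer has a cost

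*Protocol article*

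**What the plan says.** The Abstract, Participants and Study design agree on six sessions. Participants are followed "over 6 in-person exposure sessions as part of a multiple-baseline trial of 12 weeks of exposure-based CBT", the sessions "will occur at weeks 5-10 in the protocol", and "Peripheral psychophysiological data will be collected during these six in-person exposure sessions". Weeks 5 to 10 are six weekly visits, so the session 1 that carries physiology can only be the first exposure session.

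Data analysis differs. The change models use indicators "from each of the five in-person exposure sessions defined as the outcome variable to assess change over time". In the same paragraph, the three physiological measures "from session 1 will be included at both levels 1 and 2 to account for the effects of individual differences at baseline" act on both intercept and slope, "allowing us to test whether individual differences are predictive of treatment response within this model". Session averages are to be calculated over all sessions. The text neither names the session missing from the five nor says that session 1 leaves the outcome because it is the covariate.

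Hypotheses 1-3 concern change across sessions; for example, "HR will show a reduction over time between sessions, reflecting decreased arousal". On shape, "Linear, quadratic, and cubic fits will be compared to determine the best-fitting model of change over treatment". The Summary and Hypotheses section gives special attention to the response at the first exposure.

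**The concern.** Two models fit the text, and they answer different questions.

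If the count of five is a slip and all six sessions are outcomes, the session-1 value stands on both sides of the equation. A youth whose first reading is high by chance has a high predictor value and a high first point, and therefore a falling slope. The session-1-by-time term is pulled below zero with no real relation. That term is meant for inference, not only for adjustment. A negative coefficient would read as higher initial HR or EDA (or lower initial HRV) going with more change, which is close to what the Summary and Hypotheses section leads the reader to expect.

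If the five are sessions 2-6, this problem goes away. However, the slopes that test hypotheses 1-3 then start at the second exposure. The first step of change is outside them, and precision falls in a study that already reports low power.

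**Working it through.** **Inputs from the article.** Six recorded sessions; five modelled; n = 40; alpha 0.05; stated power 52.7% (hypothesis 1) and 29.7% (hypothesis 2).

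**Assumptions, because the article gives no figure.** Between-session correlation rho of 0.5 to 0.9; person-slope variance of 0 to 0.05 of residual variance; equal correlation between sessions; total SD 1; no dropout.

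**The plan's own figure.** The stated powers cannot be rebuilt, because no effect size, SD, correlation or number of sessions is given. They can only be inverted. With a two-sided normal test, 52.7% implies a noncentrality of 2.03 and 29.7% implies 1.43.

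**Reading A: session 1 is covariate and outcome (six outcomes).** Code time 0 to 5, with mean 2.5 and centred sum of squares 17.5. The least-squares slope gives session 1 the weight -2.5/17.5 = -1/7, and the other five weights sum to +1/7. With no true relation, the covariance of slope with session 1 is -1/7 + rho/7 = -(1-rho)/7. Session 1 has variance 1, so this is also the expected coefficient: -0.071 at rho 0.5, -0.043 at 0.7 and -0.014 at 0.9.

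Simulated rejection of the nominal 5% test (each person's slope regressed on session 1, n = 40, no true relation):

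| rho | slope variance 0 | slope variance 0.05 of residual |
|---|---|---|
| 0.5 | 80% | 51% |
| 0.6 | 70% | 40% |
| 0.7 | 56% | 31% |
| 0.8 | 39% | 22% |
| 0.9 | 21% | 13% |

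A smaller run of 300 replicates with a random-intercept mixed model gave 77% at rho 0.5 and 61% at 0.7 with no slope variance; some fits had convergence warnings. The test of the average slope, with session 1 centred, stayed at 4.3% to 5.4%.

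**Reading B: outcomes are sessions 2-6.** The session-1-by-time coefficient is centred on zero and its test rejects about 5% of the time. The cost falls on the slope:

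- The centred time sum of squares drops from 17.5 to 10. With residual variance 1 and slope variance k, the SE ratio is sqrt[(k + 1/10)/(k + 1/17.5)].
- k = 0: sqrt(17.5/10) = 1.32.
- k = 0.02: sqrt(0.1200/0.0771) = 1.25.
- k = 0.05: sqrt(0.1500/0.1071) = 1.18.
- A drop of 1 SD from session 1 to 2 followed by a plateau gives a linear slope of -2.5/17.5 = -0.143 SD per session with six outcomes, and exactly 0 with sessions 2-6.
- If the stated powers assumed six sessions and the same per-session slope, then at k = 0 the noncentralities become 2.03/1.32 = 1.53 and 1.43/1.32 = 1.08. Power is then about 33.5% for hypothesis 1 and 18.9% for hypothesis 2.

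**The case against.** The strongest reply is that six sessions minus one baseline leaves five, so the literal text is an ordinary baseline-adjusted model of sessions 2-6, and the inflated rejection rates describe a model that the article does not state. This is a fair reading, and perhaps the more natural one. But nothing in the article confirms it, and it carries its own cost for hypotheses 1-3.

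Four stronger inferences are tempting and not supported.

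- **The tests of hypotheses 1-3 are biased.** They are not. The artefact falls on the session-1-by-time term, and the average slope is unbiased when session 1 is centred. Data analysis states centring only for the CGI model, so it should also be stated here. The CGI-outcome models are also free of the artefact, because session-1 physiology is not part of the CGI.
- **The baseline-prediction test would usually be significant by chance.** This depends on rho and slope variance, neither of which is given. Rejection exceeds 50% only in the lower-correlation cases. The Bonferroni-Holm correction may reduce it further, but its scope is not stated.
- **Entering session 1 at both levels duplicates a column.** The sentence goes on to name intercept and slope. The natural meaning is a level-2 main effect plus a cross-level interaction with time, which are distinct and estimable. A session-1 value is constant within a person, so the level-1 label is loose, but the model is not unidentifiable.
- **A known share of the change is lost under reading B.** That needs a habituation curve, which the article does not give. It stresses the level at first exposure and plans nonlinear fits, but does not say that change is concentrated between sessions 1 and 2. That step can also still be estimated as the session-2 model mean minus the session-1 mean.

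**Conclusion.** The point stands in this form. The article contradicts itself on the number of outcome sessions and leaves the role of session 1 open. Under one reading, the test of baseline physiology as a predictor of physiological change has a false-positive rate of about 13% to 80% instead of 5%. The direction of the bias follows from the algebra; its size rests on the assumed rho and slope variance. Under the other reading, that test is sound, but the slopes for hypotheses 1-3 omit the first change and their standard error is about 18% to 32% larger. The power loss shown applies only if the stated figures assumed six sessions. The choice should be fixed before analysis, since making it afterwards could change the results.

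**What to change.** Reconcile five with six and name the outcome sessions. Then separate two models.

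(a) For hypotheses 1-3, use all six sessions as outcomes, with random intercept and slope and no session-1 covariate; the random intercept already carries individual level.

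(b) For prediction, use centred session-1 physiology as a level-2 predictor of CGI-S or of sessions 2-6 only, with a main effect and a cross-level interaction with time. Alternatively, report the intercept-slope covariance from (a).

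Replace the reference to both levels with the wording in (b). State in Sample size and power analysis how many sessions the power figures assume. If the authors prefer a centred session-1 covariate with sessions 2-6 throughout, that is defensible, provided that they say so and report the session 1-to-2 change separately.

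The cost is analysis wording and one sentence on power; no new data are needed.
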